#### Outcome Data

##### PCWs Data

PCWs will be interviewed by a member of the research team during a 1-week period at each PHC clinic at 4 time points: (1) before mhGAP-IG training, (2) immediately post training, (3) 3 months post training, and (4) 8 months post training. During the research interviews, all PCWs will complete quantitative assessments, assessing 5 variables related to the PCW outcomes:

1. mhGAP-IG Knowledge Scale: In the mhGAP-IG training, knowledge is assessed by a standardized set of 30 questions in the multiple-choice question format, the mhGAP-IG Knowledge Scale. These are administered before and after training to measure the change in knowledge.
2. Revised-Depression Attitude Questionnaire (R-DAQ): Previously used in both Nepal and Nigeria, the R-DAQ [\[40\]](#) assesses clinicians' views and understanding of depression. The R-DAQ 22-item scale asks clinicians to rate each item as *strongly disagree*, *disagree*, *neither disagree nor agree*, *agree*, or *strongly agree*. Examples of items include "depression is a disease like any other (eg, asthma, diabetes)," "psychological therapy tends to be

unsuccessful with people who are depressed,” and “becoming depressed is a natural part of being old.”

3. Social Distance Scale (SDS): The SDS was designed by Bogardus [41] to measure the level of acceptability of various types of social relationships between Americans and members of common ethnic groups [42,43]. The modified SDS has been widely used to measure mental health-related stigma and to understand the importance of labels attached to people with former mental illnesses [42,44]. The modified version consists of 12 items that represent social contact with different degrees of distance. The SDS measures the acceptability of different degrees of social distance and thus, by inference, the attitude of the respondent to the person with the condition [45]. The SDS sum score represents the attitude of the respondent toward the condition. The SDS has been used in global mental health research. Among stigma measures, it has been shown to be most strongly associated with health worker competence [46].
4. The Enhancing Assessment of Common Therapeutic Factors (ENACT)-clinician version: The ENACT-clinician version [47] is a measure of therapist competence that has been developed for use in training and supervision across settings varied by culture and access to mental health resources. A version adapted for mhGAP-IG trainings focusing on depression was used, with competencies rated on a 4-point scale from potentially harmful to done well, with good reliability ( $\alpha=.89$ ). Examples of items include “non-verbal communication, active listening,” “assessment of functioning & impact on life,” and “explanation and promotion of confidentiality,” among others.
5. Perceptions of Supervisory Support Scale (PSS): Supervision quality will be assessed using the PSS [48]. The PSS is a 19-item scale that assesses perceived support. Subscales include emotional support, support for client goal achievement, and professional development support. Each item is rated using a 5-point Likert scale. Additional information about supervision quality will be collected through qualitative interviews with health workers at the last data collection time point.

## Patient Data

In the month before mhGAP-IG training, the research team will collect depression diagnosis and treatment initiation data from patient baseline interviews and clinical notes at participating clinics. These data will be used as a baseline assessment of the accuracy of diagnosis and the adequacy of treatment initiation. Patients attending PHC 3-8 months following PCW mhGAP-IG training will be interviewed by a trained member of the research team either immediately before or after their clinic appointment. Quantitative measures will be used to assess depression, disability, intervention acceptability, and therapeutic alliance during individual interviews with a member of the research team as follows:

1. Depression: The PHQ-9 [49] is a self-administered diagnostic instrument for depressive disorders. The *Diagnostic and Statistical Manual of Mental Disorders, Fourth Edition* criteria for depression are scored as 0 (not at all) to 3 (nearly every day). A PHQ-9 score  $\geq 10$  had a sensitivity of 94% and 85% and a specificity of 80% and 99% for major depression in Nepal [50] and Nigeria [51], respectively.

2. Disability: Data on sociodemographic information (sex, age, education, marital status, and work status) will be collected through questions A1-A5 of the World Health Organization Disability Assessment Schedule 2.0 (WHODAS 2.0) [52]. The WHODAS 2.0 is a generic assessment instrument assessing health and disability across 6 domains (cognition, mobility, self-care, getting along, life activities, and participation). The research team will use the 12-item interviewer-administered version. The WHODAS 2.0 has been adapted and validated for use in Nepal [53-55] and Nigeria [56].
3. Treatment initiation: Treatment details will be extracted by the research team from patient records to document how diagnosis matches up with treatment and treatment modifications during care.
4. Therapeutic alliance: The ENACT-service user version [47] is a 15-item measure of patient experience of care and perception of therapeutic engagement. Example items include clear explanations, names for health problems, understanding and empathy, and expectations for recovery.
5. Suicidal ideation and behavior: Suicidal ideation and behavior will be assessed, in Nepal only, using suicidality questions adapted from the Composite International Diagnostic Interview suicidality module [57]. This tool has been widely used in Nepal [58]. We will ask participants whether they had thought of taking their own life in the past 12 months. Those who will respond affirmatively to the ideation question will be asked if they had made a plan to take their own life. In Nepal, those who meet the criteria for current suicidal thoughts or those who attempted suicide in the past 3 months will be immediately referred to a trained psychosocial counselor. In Nigeria, patients endorsing the suicidal ideation item from the PHQ-9 will receive further assessment of suicide risk in line with local protocols.

Confirmation of diagnosis and treatment initiation will be collected from the clinical notes by PCWs. Patients interviewed in the first 3 months of data collection and who screen positive for depression will be invited to participate in a follow-up interview 3 months after their first appointment. The interview will consist of quantitative assessments of depression (PHQ-9), disability (WHODAS 2.0), therapeutic alliance (the ENACT-service user version), and suicide ideation and action Composite International Diagnostic Interview. Treatment details will be extracted by the research team from patient records to document treatment retention.

#### Measure Translation and Adaptation

All standardized measures, except for the AIM, IAM, FIM, ORIC, NoMAD, and PSS (Nigeria only), have been translated and culturally adapted in Nepal and Nigeria. Psychometrics for translated and validated (when appropriate) measures are provided in the descriptions above. Within each site, where measures have not yet been adapted and validated, the International Test Commission Guidelines for Translating and Adapting Tests [59] will be followed, including cognitive interviewing [60,61] and the assessment of content validity.

#### Analysis

#### Implementation Outcome Analysis

Quantitative data will be assessed using generalized linear mixed models, depending on the distribution of the outcome (continuous, binary, and count). Descriptive statistics of the implementation survey data (FIM, AIM, and IAM) will be provided. The association between the primary outcome (changes in the PHQ-9 detection rate) and implementation survey data will be analyzed using linear mixed models at 3 and 8 months post training. A 2-level hierarchical model will be used, and all time points will be included as repeated measures in the model at baseline and at 3 months post training and 8 months post training to improve power and account for clustering of observations at patient and PCW levels. These models use maximum likelihood estimation and thus allow for missing outcome data under the missing at random assumption. Associations between secondary outcomes (eg, knowledge, attitudes, and competency) and implementation survey data will be assessed with a similar methodology for the primary outcomes, using generalized linear mixed models depending on the type of outcome (eg, normal, binary, and count). All analyses will be conducted using STATA V.15.1. (StataCorp).

Qualitative data will be assessed using thematic analyses [62]. Thematic analysis consists of 5 stages: familiarization, generating codes, constructing themes, revising themes, and defining themes [63]. Draft codebooks for each participant group (eg, PCWs, supervisors, and patients) will be developed on an initial subset of transcripts by 2 researchers at each site. Following refinement based on researcher consensus, the final codebooks will be used to code each transcript independently by 2 researchers at each site. Subcategories will be assessed for the number of occurrences across all transcripts and themes and categories relevant to the data identified. The findings will be triangulated with quantitative data on implementation and provider and patient outcomes to assess the feasibility and impact of the e-mhGAP-IG.

#### PCW and Patient Outcome Analysis

The primary outcome will be the accuracy of the depression diagnosis. The research team will identify a patient as screening positive based on the PHQ-9 result immediately before or after the patient sees the PCW. *Screening positive* will be defined as scoring  $\geq 10$  on the PHQ-9. The research team will also assess sensitivity to change, for change in both the PHQ-9 and WHODAS 2.0 scores from baseline and 3 months after initiation of treatment. *Positive diagnosis* will be defined as a clinical diagnosis of depression documented by the health worker in the clinical notes. *Accurate detection* will be defined as PHQ-9  $\geq 10$  and a health worker depression clinical diagnosis. We will also report findings in terms of the sensitivity and specificity of health worker diagnoses. *Sensitivity* will be defined as the proportion of health worker–diagnosed patients who had PHQ-9 above the cutoff, out of all patients who scored above the PHQ-9 cutoff. *Specificity* will be defined as the proportion of patients who did not receive a health worker depression diagnosis and scored below the PHQ-9 cutoff, out of all patients scoring below the PHQ-9 cutoff.

Features of the cRCT design will be accommodated in all analyses, and an intention-to-treat approach will be used. The principles of analysis will be (1) the PHC-level accuracy outcome is binomial (ie, number of accurate diagnoses out of all diagnoses based on patient-level data), and therefore, a generalized linear mixed model will be used (specifically, a log-binomial regression to obtain probability ratios); (2) accuracy is a cumulative measure, and therefore, there are no repeated measures over time; and (3) missing data can occur at either the health worker or patient level.

Differences in detection rates will be assessed using patient outcome data at 3 months after enrollment, only in depression cases identified in each arm (ie, scoring  $\geq 10$  on the PHQ-9), and the health worker clinical diagnosis. A 3-level hierarchical model will be used when all time points will be included as repeated measures in the model to improve power and take into account clustering of the observation at patient and PHC levels. The 3-level linear mixed model will be used to estimate a 95% CI for the comparison of clinical diagnosis and PHQ-9 screening positive rates (as well as a subanalysis with PHQ-9 plus WHODAS 2.0 criteria) within electronic and paper mhGAP-IG versions. Secondary outcomes (eg, knowledge and attitudes) will be assessed within each arm with a similar methodology for the primary outcomes, using generalized linear mixed models depending on the type of outcome (normal, binary, and count). Clinical feasibility will also be triangulated using penetration and costing data.

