## Participants

An estimated 20 PHCs in Nepal and 6 PHCs in Nigeria will be identified by local partners. Clinic managers and PCWs will be approached by local research staff with invitations to participate in the study. On the basis of the staffing of PHCs, we estimate that 2-5 PCWs per PHC will participate, equivalent to 40 PCWs in Nepal and 30 PCWs in Nigeria, approximately 15-20 health workers per arm per country (Figure 2).

Figure 2.

[figure not shown]

Emilia (E-mhGAP Intervention Guide in Low- and Middle-Income Countries: Proof-of-Concept for Impact and Acceptability) flow chart. e-mhGAP-IG: electronic Mental Health Gap Action Programme Intervention Guide; mhGAP-IG: Mental Health Gap Action Programme Intervention Guide.

PCWs will be eligible to participate if they are employed by the PHC or government and have roles and responsibilities related to the use of the mhGAP-IG (eg, direct clinical use or supervision). All relevant PCWs, regardless of individual study participation, will receive training in the mhGAP-IG v2.0 (electronic or paper version) and have ongoing remote support and supervision by health care providers with enhanced mental health knowledge.

Patients presenting to primary care will be enrolled in the study to evaluate their perceptions of services and to obtain descriptive information on detection rates and treatment impact to inform a

subsequent fully powered cRCT. There will be 2 periods of patient enrollment: *pre training*, which is before PCWs receive mhGAP-IG training, and *post training*, which is after PCWs have received mhGAP-IG training. For the 1-month before the mhGAP-IG training, a random selection of adults presenting to primary care will be screened by research assistants to determine depression status, which will be compared with documented diagnoses by the PCWs. Similarly, beginning at 3 months post training, a random selection of patients will be screened by research assistants for depression status. This posttraining patient enrollment will last a minimum of 3 months.

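### Follow-up patients are chosen on one PHQ-9 of 10 or more and their change is measured from that same score, so part of any within-arm fall is regression to the mean

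*Protocol*

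**What the plan says.** **Who is followed up.** Protocol, Outcome Data, Patient Data: "Patients interviewed in the first 3 months of data collection and who screen positive for depression will be invited to participate in a follow-up interview" three months after the first appointment. In PCW and Patient Outcome Analysis, screening positive "will be defined as scoring $\geq 10$ on the PHQ-9", and it rests on one measurement: "The research team will identify a patient as screening positive based on the PHQ-9 result immediately before or after the patient sees the PCW". No confirmatory score and no separate post-selection baseline is described.

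**What is measured.** The same instrument is repeated: "The interview will consist of quantitative assessments of depression (PHQ-9), disability (WHODAS 2.0), therapeutic alliance" and suicidality. The analysis section states: "The research team will also assess sensitivity to change, for change in both the PHQ-9 and WHODAS 2.0 scores from baseline and 3 months after" treatment begins.

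**How it is analysed.** The last paragraph of PCW and Patient Outcome Analysis says: "Differences in detection rates will be assessed using patient outcome data at 3 months after enrollment, only in depression cases identified in each arm", that is, PHQ-9 of 10 or more. It enters all time points as repeated measures and estimates a confidence interval for the "comparison of clinical diagnosis and PHQ-9 screening positive rates" within each mhGAP-IG version.

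**What it is for.** Participants: patients are enrolled partly to "obtain descriptive information on detection rates and treatment impact to inform a" later, fully powered trial. Objective 6 in Aims and Objectives is to describe depression treatment outcomes.

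**A conflicting rule.** Implementation Data, Patient Data, instead takes the follow-up group from patients whom a health worker diagnosed with depression. The Health Economic Analysis section says that patient outcomes are not measured in the study at all.

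**The concern.** When people are selected because a fluctuating score was high on one day, their average on the next occasion is expected to be lower, treated or not. Here the selecting score also serves as the baseline from which change is taken. A fall in PHQ-9 within either arm therefore mixes three things: any treatment effect, natural recovery, and regression to the mean. The plan has no element that separates them within an arm.

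Two descriptive results are at stake. A raw fall could be reported as treatment impact, although some fall would occur with no effect. The same fall could be taken as evidence that the PHQ-9 is sensitive to change. Any positive rate followed over time in this cohort would have the same fault in its plainest form, because it is 100% at entry by construction and can only go down.

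**Working it through.** The protocol gives no expected figure for change at follow-up. Its only power figure, 90% for a rise in detection from 10% to 53%, concerns the index visit. It is reproduced approximately with 20 patients per period: SE = √[(0.10×0.90 + 0.53×0.47)/20] = 0.130, and Φ(0.43/0.130 − 1.96) ≈ 91%, before the small clustering correction. Nothing below depends on it.

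**1. Repeat-positive rate from the protocol's own figures**

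Inputs: for PHQ-9 ≥10, sensitivity 94% and specificity 80% in Nepal, 85% and 99% in Nigeria (Outcome Data, Patient Data); prevalence 16.8% among primary care attendees in Nepal and 5.5% in Nigeria (Settings). The 5.5% is not stated to be a rate among attendees, so using it here is an assumption.

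Formulas, with true status unchanged and errors independent between occasions:
- P(positive) = Se×p + (1−Sp)×(1−p)
- PPV = Se×p / P(positive)
- P(positive again) = PPV×Se + (1−PPV)×(1−Sp)

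Nepal:
- P(positive) = 0.94×0.168 + 0.20×0.832 = 0.324
- PPV = 0.158/0.324 = 0.487
- P(positive again) = 0.487×0.94 + 0.513×0.20 = **0.56**

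Nigeria:
- P(positive) = 0.85×0.055 + 0.01×0.945 = 0.0562
- PPV = 0.0468/0.0562 = 0.832
- P(positive again) = 0.832×0.85 + 0.168×0.01 = **0.71**

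With no true change, the rate falls from 100% by 44 points in Nepal and 29 in Nigeria. If a patient's errors are correlated between occasions, the fall is smaller.

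**2. Mean fall and repeat-positive rate from a normal model**

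The protocol gives neither an SD nor a 3-month correlation r. Assumed ranges: SD 4 to 6, r 0.6 to 0.9. With z the cut-off for the positive rates in step 1, and λ = φ(z)/P(positive):
- Nepal: z = 0.456, λ = 0.3596/0.3243 = 1.109
- Nigeria: z = 1.588, λ = 0.1131/0.0562 = 2.013
- Mean fall = SD×(1−r)×λ
- SD of change = SD×√[(1−r)²×(1+λ(z−λ)) + 1−r²]
- Standardised response mean (SRM) = mean fall / SD of change

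The lowest value is Nepal, SD 4, r 0.9: 4×0.1×1.109 = 0.44. The highest is Nigeria, SD 6, r 0.6: 6×0.4×2.013 = 4.83.

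| r | Nepal: mean fall | SRM | positive again | Nigeria: mean fall | SRM | positive again |
|---|---|---|---|---|---|---|
| 0.6 | 1.77–2.66 | 0.54 | 59.3% | 3.22–4.83 | 0.99 | 32.2% |
| 0.7 | 1.33–2.00 | 0.45 | 65.0% | 2.42–3.62 | 0.84 | 40.4% |
| 0.8 | 0.89–1.33 | 0.36 | 71.6% | 1.61–2.42 | 0.67 | 50.6% |
| 0.9 | 0.44–0.67 | 0.25 | 80.1% | 0.81–1.21 | 0.46 | 64.5% |

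The SRM only puts the fall on a common scale; the protocol names no responsiveness statistic.

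**3. Check on shape**

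A simulated skewed score bounded at 0 to 27, with positive rates of about 25%, 14% and 6% and the same r, gives mean falls of 0.9 to 5.2 points and 77% down to 32% positive again. The result does not depend on normality.

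Steps 1 and 2 disagree on which country is more affected: Nepal by the accuracy figures, Nigeria by the normal model. They support the existence and rough size of the artefact, not a ranking of the countries.

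**The case against.** The case against has real force on several points.

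- **Selection rule.** The Implementation Data section follows diagnosed patients, and the change measure is timed from the start of treatment. Entry through a diagnosis as well as the score would weaken the artefact. This stands as a limit on size. It does not remove the artefact, because the analysis section still restricts to PHQ-9 of 10 or more.
- **The positive rate as an outcome.** A reader might infer that the plan tracks who is still positive at 3 months. It defines no such outcome. The paragraph opens with detection, and comparing clinical diagnosis with PHQ-9 status is the more natural reading. The wording is loose enough to need closing off, but no more can be claimed.
- **The full trial.** A reader might infer that an inflated effect would be carried into the full trial. The documents do not support this: that trial's primary outcome is accurate identification of depression, no progression criterion uses PHQ-9 change, and the economic model takes patient impact from elsewhere.
- **PHQ-9 against WHODAS 2.0.** Selection acts on the WHODAS 2.0 only through its correlation with the PHQ-9, so a reader might expect a biased contest between the scales. The protocol plans no ranking of them.
- **Noise alone.** A 3-month correlation below 1 also reflects genuine fluctuation and recovery, so the whole computed fall should not be called measurement error.
- **Cancellation between arms.** If the same PHQ-9 rule selects patients in both arms, a between-arm contrast largely removes the artefact. This is correct and is the basis of the fix, but the comparisons the protocol states are within arm.

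That the result is only descriptive does not answer the point. A description offered as treatment impact still misleads if part of it would appear without treatment.

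**Conclusion.** The concern holds in a limited form. Under the Outcome Data rule, selection and baseline are the same single PHQ-9, so the within-arm fall will overstate improvement.

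On the protocol's own accuracy and prevalence figures, about 56% (Nepal) and 71% (Nigeria) would be positive again with no change. This assumes independent errors and, for Nigeria, that 5.5% applies to attendees. The mean fall is about 0.4 to 5 points and rests wholly on the assumed SD and correlation; at r = 0.9 it is modest, about 0.4 to 1.2 points. If diagnosis also governs entry, all of these are likely to be smaller.

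The results affected are the descriptive treatment outcomes and the sensitivity-to-change assessment. Index-visit detection, the progression criteria and the full trial's primary effect size are not affected.

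**What to change.** 1. In PCW and Patient Outcome Analysis, report 3-month PHQ-9 and WHODAS 2.0 as a between-arm difference, each adjusted for its own baseline score and for clustering. State that the raw within-arm fall will not be presented as treatment impact or as evidence of sensitivity to change. Baseline adjustment within a single arm would not remove the regression from the average fall; the between-arm contrast is what helps.
2. In the last paragraph of that section, state that the PHQ-9 positive rate is not an outcome in a cohort restricted to PHQ-9 of 10 or more.
3. As a sensitivity analysis only, show beside the observed fall the fall expected from regression to the mean, (1−r) × (mean of selected patients − mean of all screened patients), for r of 0.6 to 0.9. The trial already collects both means. The term varies fourfold over that range (0.4 against 0.1), so it illustrates and does not correct.
4. Reconcile the follow-up selection rules in the Implementation Data and Outcome Data sections, and the Health Economic Analysis statement that patient outcomes are not measured. This bears on item 1: if diagnosis governs entry, and the tool changes who is diagnosed, the two arms' cohorts are no longer selected alike.

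**Cost.** Wording and one extra calculation; no new visit, patient or instrument. The apparent improvement becomes smaller, r has to be assumed, and the between-arm estimate will be imprecise in a feasibility trial.

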## Methods

### Settings

The study will take place within the administrative districts of Nepal (Jhapa administrative district) and Nigeria (Ibadan North, Ibadan North West, Ona Ara, and Akinyele local government areas). In each country, a minimum of 6 PHCs will be recruited for the study to represent a range of urban and rural settings.

Nepal is classified as a lower-middle-income country, with an estimated population of 28.1 million [19]. In a recent survey, 16.8% of individuals attending primary care facilities met the criteria for depression [20]. However, only 8.1% had sought care for their mental health [21]. Primary care facilities include PHCs, health posts, urban health centers, community health units, and primary

health care outreach clinics. In these facilities, services are delivered by medical officers, health assistants, staff nurses, auxiliary health workers, and auxiliary nurse midwives. However, medical officers and staff nurses are only available in PHCs [22]. The availability of mental health care in the country is limited to services largely provided through hospitals located in the larger cities [22]. The Jhapa administrative district has a total population of 812,650 people. Medical care is provided through 1 zonal hospital, 6 PHCs, 44 health posts, and 6 urban health centers [23]. Specialist outpatient mental health services are located in 2 private hospitals within the district. The mhGAP-IG was adopted by the government of Nepal and implemented in several districts after the major earthquake in 2015. The government has allocated a budget for district-level mental health care services to include the addition of 6 psychotropic drugs to those already freely available within health facilities and the strengthening of community mental health care services [24].

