## Statistical Power and Sample Size Calculation

The study will take place in 1 government administrative region in Nepal and 4 in Nigeria. We will identify approximately 20 PHCs in Nepal and 6 in Nigeria. In each country, half of the PHCs will be randomly allocated to either the e-version or the paper version of the mhGAP-IG. As the clinics vary in size, we will assess at least two staff members in each clinic, with an estimated 2-5 health workers per facility and an overall enrollment of 40 PCWs in Nepal and 30 PCWs in Nigeria. Regarding patient numbers, on the basis of the sample size for the study by Sangha et al [34] on smartphone app for improving cognition to improve case detection, we will conduct within-arm comparison detection rates if at least 40 patients screen positive on the Patient Health Questionnaire (PHQ-9) in the research assistant interview in the 1-month pretraining period and in the first month of the posttraining patient enrollment period, which begins after 3 months of intensive supervision. This will allow us to detect a within-arm increase in the clinical case identification rate of 43% for the e-mhGAP-IG after the implementation of the e-version with 90% power at the 5% level of significance, assuming an intraclass correlation coefficient of 0.02. For example, with a 10% detection rate pretraining, 2 patients would receive a health worker depression diagnosis out of 20 patients screening positive. After training, the detection rate would increase to 53%, which equates to 11 patients diagnosed by a health worker out of 20 patients screening positive.

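### Detection scored against PHQ-9 ≥10 measures agreement with a screen, not diagnostic accuracy: on the protocol's own figures an error-free health worker would score only about 49% in Nepal

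*Protocol*

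**What the plan says.** The Protocol's section PCW and Patient Outcome Analysis makes accuracy of the depression diagnosis the outcome and fixes the reference: "Accurate detection* will be defined as PHQ-9 $\geq 10$ and a health worker depression clinical diagnosis". PCW sensitivity is taken "out of all patients who scored above the PHQ-9 cutoff", and PCW specificity is taken among patients below the cutoff. Later in the same section, patients scoring 10 or more are treated as cases, because differences in detection are to be assessed "only in depression cases identified in each arm". The Abstract names accurate identification of depression as the primary outcome of the later full trial.

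Under Outcome Data, Patient Data, the protocol reports that the same cutoff "had a sensitivity of 94% and 85% and a specificity of 80% and 99% for major depression in Nepal" and Nigeria respectively, that is, 94%/80% in Nepal and 85%/99% in Nigeria. Under Settings, it states for Nepal that "16.8% of individuals attending primary care facilities met the criteria for depression", and for Nigeria it gives a depression prevalence of 5.5%. The worked example under Statistical Power and Sample Size Calculation starts from 10% detection among screen-positives and continues: "After training, the detection rate would increase to 53" per cent.

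The protocol describes no diagnostic interview and nowhere mentions PHQ-9 misclassification in the analysis.

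**The concern.** If the reference is wrong for a sizeable share of patients, agreement with it is not accuracy. A PCW who correctly leaves a screen-positive non-case undiagnosed is charged with a miss. A PCW who wrongly diagnoses that patient is credited with accurate detection. The size of this effect depends on the PHQ-9 error rates and on prevalence, and the protocol gives different values of both for the two countries.

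Three uses of the figure are affected: what this study can say about diagnostic accuracy, the outcome handed to the full trial, and the Health Economic Analysis, which takes the study's detection rate as the number of cases found and attaches treatment benefit to it.

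**Working it through.** **1. The plan's own figure.** Power for 10% against 53%, 20 screen-positives per period, two-sided 5% (sidedness is not stated), unpooled variance, ICC 0.02 and 2 patients per clinic: design effect 1 + (2 − 1) × 0.02 = 1.02; standard error √[(0.10×0.90 + 0.53×0.47) × 1.02/20] = 0.1315; 0.43/0.1315 − 1.96 = 1.31; power 90.5%. The stated 90% is reproduced (a pooled-variance test without the design effect gives 86.2%). What follows concerns what the 53% measures, not the power.

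**2. Inputs.** Nepal: prevalence p = 0.168, sensitivity Se = 0.94, specificity Sp = 0.80. Nigeria: p = 0.055, Se = 0.85, Sp = 0.99. Assumption: these prevalences are true prevalences among the patients screened.

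**3. Positive predictive value.** PPV = p·Se / [p·Se + (1 − p)(1 − Sp)]. A PCW who diagnoses only true major depression cannot score above the PPV among screen-positives.
- Nepal: 0.1579 / (0.1579 + 0.1664) = 0.1579/0.3243 = 48.7%; 51.3% of screen-positives are not major depression.
- Nigeria at 5.5%: 0.04675 / (0.04675 + 0.00945) = 83.2%.
- Nigeria at Nepal's 16.8%: 0.1428 / (0.1428 + 0.0083) = about 94%.

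The contrast between countries therefore does not depend on the Nigerian prevalence.

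**4. How far the Nepal ceiling moves.**

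| Varied | Range | Ceiling |
|---|---|---|
| Prevalence (Sp 80%) | 12% to 22% | 39% to 57% |
| Specificity (p 16.8%) | 75% to 85% | 43% to 56% |

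It reaches 53% at a prevalence of about 19.4%, or at a specificity of about 83.2%.

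**5. Against the 53%.** The excess over the Nepal point value is 53 − 48.7 = 4.3 points, about 1 patient in 20. The share of screen-positive non-cases that must be diagnosed to score 53% is (0.53 − 0.487·s)/0.513, where s is the PCW's sensitivity for true cases: 8.4% at s = 1, 27% at s = 0.8, 46% at s = 0.6.

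**6. Can the measure rank two guides wrongly?** In Nepal, a guide finding 80% of true cases with no false diagnosis scores 0.8 × 48.7% = 39%. One finding 60% and labelling 46% of the screen-positive non-cases scores 0.6 × 48.7% + 0.46 × 51.3% = 53%. The second looks better.

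**7. Could the rate simply be corrected?** Under conditional independence, the diagnosis rates in PHQ-9-positives and PHQ-9-negatives give two equations in PCW sensitivity S and false-positive rate F: D⁺ = 0.487·S + 0.513·F and D⁻ = 0.015·S + 0.985·F. The 0.015 is 0.168 × 0.06/(1 − 0.3243). Observed 40% and 2% solve to S = 81%, F = 0.8%. Observed 53% and 2% give S of about 108%, and 40% and 1% give a negative F. The correction is too unstable to be the main estimate.

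**The case against.** This is a feasibility trial. Its primary outcomes are feasibility and acceptability, detection rates are to be described, and no progression criterion uses them. Every term is openly defined against the PHQ-9. PCW specificity is also reported among PHQ-9-negatives, who on the Nepal figures are 98.5% free of major depression, so indiscriminate diagnosis would show there. The modelling principle counts accurate diagnoses out of all diagnoses, which penalises diagnoses in PHQ-9-negatives. A subanalysis adding WHODAS 2.0 criteria is planned. All of this stands, and it lowers the urgency. None of it reaches the gap: specificity below the cutoff cannot see wrong diagnoses above it, the all-diagnoses measure still counts those as accurate, and disability does not establish a diagnosis.

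The inputs are also uncertain. The protocol does not say how the 16.8% was measured. If it were itself a PHQ-9 ≥10 rate it could not coexist with 80% specificity: (0.168 + 0.80 − 1)/(0.94 + 0.80 − 1) = −4%. It describes attenders generally, whereas only those attending for a new case are screened. The 5.5% is not stated to be for clinic attenders, and the title of the cited Nigerian validation study names university students. These points justify ranges rather than a single ceiling.

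A reader might infer that reaching 53% in Nepal requires over-diagnosis. The documents do not support that. The 53% is introduced as an example and not tied to Nepal, and the 4.3-point excess disappears with small changes in prevalence or specificity. The stated error rates are for major depression, while the outcome is any documented depression diagnosis. A diagnosis in a patient without major depression is therefore not shown to be wrong. Nor does the protocol say that the two countries will be pooled.

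**Conclusion.** The concern holds as a fault in the outcome definition and its label. On the protocol's own values, PHQ-9 ≥10 caps an error-free PCW at about 49% in Nepal (39% to 57% over prevalences of 12% to 22%), against about 83% to 94% in Nigeria. Equal diagnostic performance would thus yield clearly different rates in the two countries, and the illustrative 53% lies close to or above what correct diagnosis of major depression alone could produce in Nepal. The measure is agreement with a screen; calling it accuracy goes beyond what it can show. This rests on the stated PHQ-9 error rates applying to the screened patients, on the quoted prevalences being true prevalences, and on major depression as the target. It does not prove over-diagnosis.

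**What to change.** - In PCW and Patient Outcome Analysis, describe the measure as agreement with, or detection among, PHQ-9 screen-positives. Stop calling screen-positives depression cases.
- Report the rate separately by country.
- In Statistical Power and Sample Size Calculation, state each country's approximate ceiling and its assumptions beside the 53%.
- Add a misclassification analysis as a sensitivity analysis, not as a replacement main estimate. Run it over ranges of PHQ-9 sensitivity, specificity and prevalence, constrain estimates to between 0 and 1, and state the conditional-independence assumption. That assumption is open to doubt, because symptomatic patients without major depression may be flagged by both the PHQ-9 and the PCW.
- Carry the resulting range into the detection input of the Health Economic Analysis.

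The cost is wording and a modest calculation on data already collected. The downsides are wider intervals, reliance on external error rates and a less favourable headline label.
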